### Ethics and registration

Upon registration to MacPLUS FS, users will consent to participate in its evaluation. Namely, they will agree that their use of MacPLUS FS will be measured for frequency and type of use, and that they will receive periodic online evaluation questionnaires. No individual identifiers will be stored in the monitored databases. The Hamilton Integrated Research Ethics Board has approved this project (REB Project #05-186), as well as a specific waiver for additional informed consent for registrants to be randomized to the different interventions, as no risk is involved and it is necessary to preserve blinding to provide an unbiased utilization measurement (primary outcome). The trials have been registered at ClinicalTrials.gov before randomization (ClinicalTrials.Gov NCT02038439).

### Trial administration and data management

The trials will be conducted at the Health Information Research Unit, at McMaster University, which designed and is hosting MacPLUS FS. Before the trials start, research staff [name] and the principal investigator [name] will check eligibility criteria of the registrants, verify their affiliation to McMaster, profession and training level, and crosscheck the information stated at registration with official administrative medical databases.

The administration of interventions, outcome measurements, and the sending of periodic online IAM questionnaires will all be programmed before randomization and further handled automatically as they will be built into the MacPLUS FS online infrastructure.

The trials will start simultaneously for all participants. All interactions with MacPLUS FS, including any click-through links within emails, will automatically sign participants on through their individual user account that tracks logins and use of EBM resources. Primary and secondary outcomes will be recorded from this automatic monitoring of the system, and stored in a specific and secure database within MacPLUS FS.

The research staff [name] and the principal investigator [name] will review overall utilization data collected on a weekly basis, looking for completeness of data and navigational bugs. However, no interim analysis will be performed before the trial end.

## Trial status

The trial is currently ongoing at the time of submission of this manuscript. We have not begun and will not perform any data cleaning, analysis or interim reports before the trial ends.

## Discussion

The three interventions in these two factorial randomized trials are innovative in at least three different ways. First, although widely used in other fields such as education, task management, business, or customer user-centered services, we are not aware that any of these approaches have been applied thus far to clinical evidence retrieval. Second, the interventions use web-based technology to facilitate low cost implementation at a broad scale, for all types of devices. Smartphones and tablets are transforming the way we live, practice medicine, and intuitively learn new skills [47],[48]. Third, the general framework for these interventions is based on effective models for teaching clinical skills at the point of care. These models have changed the way we teach clinical examination or diagnostic reasoning - embedded in our daily practice [30]-[34] - but have not yet been used to teach how to find current best evidence in the point of care, a skill that has nevertheless become designated `as essential as the stethoscope’ [8].

Our trials have also inherent limitations. First, although MacPLUS FS includes most top EBM resources currently widely used by clinicians (see Table 1), participants may still opt to access individual resources directly rather than through MacPLUS FS. However, although this may result in an apparent low frequency of search, the randomization should balance the distributions of such behaviors across study arms and not jeopardize the conclusion from the trials.

Second, although the validated IAM will try to capture the secondary outcomes of utility, use and perceived usefulness of the retrieved, these surveys may suffer from suboptimal response rates. Ideally, we would assess the effect on directly measured patient important outcomes, but this is beyond the feasibility of the current study, and particularly challenging at hospital-levels across a very wide array of potential clinical questions. In any event, the justification for doing a larger multi-centered trial with direct measurement of patient outcomes would be the observation of a sufficient utilization rate associated with a substantial effect on evidence use and usefulness in the present trial. By analogy with drug trials, this study would be a phase II trial.

Third, the interventions are primarily mediated through emails with direct login access to MacPLUS FS, and as such, their potential impact may be diluted in the numerous competing solicitations clinicians continuously receive through emails. Moreover, the Clinical Question Recorder (Intervention A) requires clinicians to actively record their questions. To maximize the chances they engage, we focused our efforts upstream in the user-centered design, implementation and testing of the recorder. Actual use in real life settings remains uncertain, although simply offering the intervention may also have some indirect effect on searches.

Finally, baseline data showed that search rates heavily fluctuate across time. Lower rates at certain periods (*e.g*., holidays, vacation days, or exam periods) may affect the assessment of the interventions, although utilization averaged over six months of follow-up should allow a reasonable comparison between study arms.

The main advantages of this study rely on the feasibility of the administration of the interventions and the outcomes measurements for a large number of clinicians, as these will be handled automatically in MacPLUS FS online system, with no possibility of crossover, and virtually no loss of follow-up for primary outcome data.

In conclusion, the trials will answer whether these innovations have the potential of enhancing knowledge translation through a clinician’s timely access to current best evidence. The MacPLUS FS interface allows a broad implementation for registrants, in a sustainable way, with limited additional costs. If effective, these interventions can further be broadly implemented beyond the McMaster community, using the twin version of MacPLUS FS - called ACCESSSS FS (http://plus.mcmaster.ca/ACCESSSS), and enhance the access to current best evidence for a large audience, across many top EBM resources in parallel, and tied directly to clinical questions.

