### III. Protocol of the randomized controlled trials

#### Setting and study participants

We will conduct the trials described in this protocol in the teaching hospitals and clinics affiliated with McMaster University, Ontario, Canada. This amounts to 2 major academic hospital systems, operating 10 hospitals in the Hamilton area, as well as 2 regional campuses in Niagara and Waterloo, Ontario.

Currently about 2,800 clinicians and students are registered in MacPLUS FS. The first trial will be conducted among all postgraduate trainees, and the second trial among all faculty registered in MacPLUS FS at the beginning of the trials, after exclusion of those no longer physically working at McMaster University affiliated hospitals. We will also exclude registrants who have never interacted with MacPLUS FS, either by logging in to read email alerts or to perform a search, during the last 12 months counting back from the beginning of the trials, regardless of how long they have been registered. These broad eligibility criteria reflect our choice to perform pragmatic effectiveness trials, rather than focusing only on high-frequency users. Indeed, our objective is precisely to increase the quantity and quality of searches among low-frequency users in real clinical practice. Nevertheless, we are excluding registrants with a very high probability of being unexposed or insensitive to our web-based interventions, either because they are no longer at our institution or have repeatedly ignored MacPLUS FS over a prolonged period.

By December 31, 2013, these eligibility criteria were met by 904 clinicians - 429 postgraduate and 475 faculty MDs (see Table 5) - after exclusion of 211 registrants no longer working at McMaster University, and 284 who never interacted with MacPLUS FS during the last year. About two-thirds of eligible users interacted with MacPLUS FS only through email alerts, while one-third performed at least one search in that period. About 16% of eligible clinicians work in the field of internal medicine, 32% work in family medicine, while the other half of the sample works in a wide array of other specialties (see Table 5).

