**Table 5 Tab5:** **Baseline utilization among the eligible 904 MDs during the six months prior to the trial**

	Postgraduates	Faculty	Total MD
	(n = 429*)	(n = 475*)	(n = 904*)
**Specialty type** - n (%)			
Internal Medicine	82 (19.1%)	66 (13.9%)	148 (16.4%)
Family Medicine	107 (24.9%)	184 (38.7%)	291 (32.2%)
Other Specialties	240 (55.9%)	225 (47.4%)	465 (51.4%)
**Total number of searches**	935	423	1,358
**Searches/month/user** - Mean (SD)	0.46 (1.42)	0.20 (0.83)	0.32 (1.16)
**Categories of search frequency** - n (%)			
>5 *(Super-searchers)*	8 (1.9%)	4 (0.8%)	12 (1.3%)
1 to 5 *(Regular-searchers)*	45 (10.5%)	24 (5.1%)	69 (7.6%)
<1 *(Occasional-searchers)*	89 (20.7%)	72 (15.2%)	161 (17.8%)
0 *(Alert-only-users)*	287 (66.9%)	375 (78.9%)	662 (73.2%)
**Time since last search** - n (%)			
<= 365 days	163 (38.0%)	143 (30.1%)	306 (33.8%)
>365 days	266 (62.0%)	332 (69.9%)	598 (66.2%)
**Total number of e-mail alerts read**	4,064	7,092	11,156
**E-mail alerts read/month/user** - Mean (SD)	1.65 (2.99)	2.54 (6.03)	2.12 (4.85)
**Total number of other weblogins**	1163	740	1903
**Other weblogins/month/user** - Mean (SD)	0.52 (4.10)	0.32 (2.85)	0.41 (3.50)

*Four additional participants (two postgraduates and two faculty) are missing from this count, as they registered in Jan 2014, just before the beginning of the trial.

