### Outcomes

#### Primary outcome

Our primary question is whether each intervention increases the quantity of searches to answer questions - *i.e*., search utilization (not counting logins to e-mail alerts or to access other resources). This will be measured by (i) rate of searches/month/user, (ii) and corresponding proportions of `super-searchers’ (>five searches/month), `regular-searchers’ (one to five searches/month), `occasional-searchers’ (<one search/month), and `alert-only-users’ (no searches/month). The primary outcome will be averaged over six months, but continuously recorded as participants will be signed on through their individual user account that tracks logins and use of EBM resources, down to individual keystrokes.

Table 5 shows the baseline utilization data during the six months prior to the start of the trial, from July to December 2013. Postgraduates MDs (n = 429) searched MacPLUS FS 935 times in total, corresponding to about 0.46 searches/month/user, whereas they accessed 4,064 alerts to new evidence, corresponding to 1.65 alerts/month/user, and consulted other web-resources in MacPLUS FS 0.52 times/month/user. About 66.9% of postgrads users were `alert-only-users,’ while 10.5% were `regular-searchers’ and 1.9% `super-searchers.’

The utilization patterns were different for Faculty MDs (n = 475) who searched MacPLUS FS half as much, about 423 times in total, corresponding to about 0.20 searches/month/user, whereas they accessed almost twice as many alerts to new evidence, 7,092 alerts in total, corresponding to 2.54 alerts/month/user, and consulted other web-resources in MacPLUS FS 0.32 times/month/user. About 78.9% of faculty used were `alert-only-users,’ while 5.1% were `regular-searchers’ and 0.8% `super-searchers.’

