### Secondary outcomes and questions

We will assess whether each intervention can increase the utility of the evidence retrieved (satisfaction in meeting users’ information needs, expected impact on one’s general practice), the use of the evidence (the extent of use when caring for a specific patient), and its perceived usefulness in patient care and outcomes (perceived benefits of applying the evidence for a specific patient). Utility, use and usefulness of the evidence retrieved will be assessed using an adapted version of the Impact Assessment Method (IAM) [41]-[43], which was specifically developed for assessing how clinicians use information, based on the Acquisition-Cognition-Application-Outcome Model [42]-[44]. This validated six-item questionnaire takes less than one minute to complete online and will be sent by e-mail for online completion following a pre-defined automatic algorithm. The first invitation will be sent out one month after the participant’s first online exposure to one or more interventions, with one reminder after 24 hours. The next invitation will be sent following the next search, but after a two-week delay. This process will be repeated until one filled questionnaire for a clinical question is returned, or the trial ends (see details and full questionnaire in Additional file 3). Perceived usefulness will be analyzed as the `number needed to benefit from evidence,’ defined as the number of patients for whom the evidence has to be retrieved to observe or expect health benefits for one patient [45]*.*

Other secondary questions that we plan to address include whether each intervention efficacy varies across time within the six-month trial (*e.g*., persistent, transient, increasing or decreasing effect), and whether the interventions have an impact on non-searching utilization of MacPLUS FS (*i.e*., frequency of alerts read, frequency of web logins for other clinical resources).

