### Hypotheses and statistical analysis

The two trials are separate and will be analyzed as such. We have three primary hypotheses for each trial: that the clinical question recorder will be more effective than the control; that the evidence retrieval coach will be more effective than the control; and that audit, feedback and gamification will be more effective than the control. Each of these hypotheses will be tested separately (half of the sample compared to the other half). The effect of each intervention will be tested by regressing the average number of searches per month over the trial’s six-month time period for each user onto dummy variables for each intervention, controlling for search frequency at baseline. The distribution of the number of searches per user is not known at present, but baseline data suggests excess zeros with extra-Poisson variation. We will attempt to capture the distribution parametrically, but in the event that it is not possible to do this accurately, we will use ordinary least squares to estimate the regression coefficients together with heteroscedasticity-robust standard errors.

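### Complete search logging is not complete follow-up: the plan as described cannot tell a clinician who left after randomisation from one who stayed and did not search, so a lasting effect could seem to fade on an absolute scale

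*Protocol article*

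**What the plan says.** The Discussion lists as a strength that outcome measurement is automatic, "with no possibility of crossover, and virtually no loss of follow-up for primary outcome data".

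The eligible sample was reached "after exclusion of 211 registrants no longer working at McMaster University" and of a further 284 who had not interacted with the system in the past year (Setting and study participants). The same section explains that both groups were judged very unlikely to be exposed to the interventions or to respond to them. Trial administration and data management describes how affiliation was verified against administrative databases, and places that check before the trials start. The article describes no later check.

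On the outcome, the Primary outcome section says: "The primary outcome will be averaged over six months, but continuously recorded as participants will be signed on through their individual user account". The main model is described as "regressing the average number of searches per month over the trial’s six-month time period for each user onto dummy variables for each intervention", with baseline search frequency as a covariate. If no parametric distribution fits, "we will use ordinary least squares to estimate the regression coefficients together with heteroscedasticity-robust standard errors" (Hypotheses and statistical analysis). A secondary question is "whether each intervention efficacy varies across time within the six-month trial". It is addressed by an exploratory GEE on each user's count in each of the six months, with a time-by-intervention term (Analysis of secondary questions). The link function is not given.

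The notes to Table 1 say that searching is always free, and that full text is licensed on site, with remote routes for most resources.

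**The concern.** A log with no searches in it has two possible meanings: the participant was present and chose not to search, or the participant had gone. Nothing described in the article separates the two after randomisation. Yet the protocol treats the same status as reason enough to exclude someone before randomisation.

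Two things are at stake. First, on the difference-in-means scale, months contributed by absent non-searchers pull the estimated effect toward zero. Second, and more important for interpretation, departures can only accumulate over follow-up. The trial asks whether effects persist or wear off, and growing absence can imitate wearing off.

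Timing may add to this. Four late participants are left out of the baseline count "as they registered in Jan 2014, just before the beginning of the trial", so follow-up began in or soon after January 2014 and six months end around July or August. If training years end in mid-year, which is an assumption, postgraduate departures would fall in the last month or two, exactly where a fade would be looked for.

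**Working it through.** **Inputs from the protocol.** Eligible 904 (429 postgraduates, 475 faculty); excluded as departed 211; excluded as inactive 284; follow-up six months; baseline postgraduate mean 0.46 searches/month (SD 1.42); power targets 0.9 (postgraduates) and 0.5 (faculty). The protocol gives no rate of departure after randomisation, so there is no figure of its own to reproduce on this point.

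**Step 1: does registration outlast departure?** Taking the three counts as one screened pool, 904 + 211 + 284 = 1,399, and 211/1,399 = 15.1%. So it does. The period over which these people left is not stated, and this is not a six-month rate.

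**Step 2: the six-month absolute effect.** Assume that departure is unrelated to allocation, that leavers stop searching, that their remaining months count as zero, and that the effect among those present is constant. Let d be the share leaving and r the months remaining when they leave. The proportional shrinkage is d × r/6.

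| d (assumed) | r (assumed) | Shrinkage of six-month difference | Month-6 difference multiplied by (1 − d) |
|---|---|---|---|
| 5% | 1 to 2 | 0.05 × 1/6 = 0.8% to 0.05 × 2/6 = 1.7% | 0.95 |
| 20% | 1 | 0.20 × 1/6 = 3.3% | 0.80 |
| 33% | 2 | 0.33 × 2/6 = 11% | 0.67 |

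If departures are instead spread evenly over six months, the six-month difference is multiplied by 1 − d/2 and the month-6 difference by 1 − 5.5d/6. For d = 5%, 10% and 20% these are 0.975 and 0.95, 0.95 and 0.91, and 0.90 and 0.82.

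**Step 3: the time trend.** As an illustration, take a constant true difference of 0.38 searches/month in postgraduates and d = 15% spread evenly.

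- Month 1: 0.38 × (1 − 0.15 × 0.5/6) = 0.375.
- Month 6: 0.38 × (1 − 0.15 × 5.5/6) = 0.328.

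The absolute effect appears to fall although nothing has changed among those present.

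**Step 4: the same data as a ratio.** Let p be the share still present in a month, equal in both halves. The rate ratio is (0.46 + 0.38)p / (0.46p) = 0.84/0.46 = 1.83 in every month. The share p cancels, so there is neither dilution nor fade.

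**Step 5: power.** By a two-sample normal approximation (two-sided 5%, half against half, stated SDs), power at the targets of 0.9 and 0.5 stays above 99.9% even with d = 30% spread evenly. That this exceeds the stated 80% is a separate matter. Lost power at those targets is not the argument here.

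**The case against.** The strongest reply is that the protocol never says leavers are scored as zero. That reading is inferred from a fixed six-month average and six monthly counts per user. Handling of exposure time commonly sits in an analysis plan that is not shown. This stands as a limit on the point. It does not remove it, because no analysis plan can adjust for departure dates that nobody collected, and the article describes affiliation being checked only at the start.

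Table 5 might suggest that per-user time is already used: 935/(429 × 6) = 0.36 against the stated 0.46, and 423/(475 × 6) = 0.15 against 0.20. Time since registration is one possible explanation. It would handle late joiners but not leavers, whose accounts remain open.

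Leaving also need not end searching. A reader might infer that leavers necessarily lose access to full text. The notes to Table 1 do not support that: searching is free, and remote access exists by VPN or individual subscription. The primary outcome is searches in any case. Some leavers may go on searching and be logged.

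A reader might also infer that leavers swell the alert-only category. Someone who goes with one or two months remaining has four or five months of logged use, and would seldom be moved into that category.

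Finally, keeping everyone as randomised is normal in a pragmatic trial, a parametric model is planned before least squares, and the time-trend analysis is labelled exploratory. All of this is right, and it is why the primary comparison is not in question.

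**Conclusion.** The point holds in a limited form. The follow-up claim is accurate for capture of searches, but the plan as described cannot separate departure from non-use.

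The as-randomised six-month comparison remains valid. With departure unrelated to allocation, the consequence is attenuation on the absolute scale, not a spurious benefit. A reader might take the point as bias in the primary result or as a serious loss of power. The documents support neither.

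The dilution is modest: about 1-2% if 5% leave with one to two months remaining, and 3-11% if 20-33% do. The consequence that matters more is a constant effect appearing to fall by roughly the share departed in the exploratory monthly analysis. Both depend on assumed departure rates, on leavers ceasing to search, on their later months being counted as zero, and on an absolute scale. A rate ratio would be spared, and the protocol does not fix the scale. The only departure figure in the document, 15.1%, covers an unstated period and cannot stand in for a rate during the trial.

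**What to change.** 1. At trial end, and before allocation is revealed, repeat the affiliation check described under Trial administration and data management for every randomised participant, and record departure dates.
2. Keep the as-randomised six-month analysis as primary, unchanged.
3. In the exploratory time-trend model, treat months after departure as not at risk, or show the results with and without those months. The second option also covers leavers who kept searching.
4. Report the number of departures by arm, and limit the Discussion statement to complete automatic capture of searches.

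This is still practicable: Trial status says that no cleaning or analysis has begun, and Randomization says that allocation is concealed from the analysts. The cost is one repeat of an administrative check already done once, a small change to an exploratory model, and a follow-up statement that reads less favourably. If few participants left, the count will support the present claim.
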